### Sensitivity analyses for primary outcome

#### Method of accounting for missing data

We will perform three sensitivity analyses for the primary outcome to assess the robustness of the results to other methods of account for missing data [32]. The first sensitivity analysis involves specifying a different imputation model than that used in the primary analysis, and the last two sensitivity analyses involve the re-analysis of the primary outcome using two approaches which are not based on MI.

The sensitivity analyses are:

1. We will determine which baseline covariates are associated with loss to follow-up and include them in the imputation model. The analysis model will be the same as that for the primary analysis, except for the inclusion of additional covariates (that is, those that we determined were associated with loss to follow-up) in the imputation model.

2. We will perform a complete case analysis, where all participants who did not complete all components of the CPG disability score at 12 months will be excluded from the analysis. The analysis model will be the same as that for the primary analysis, except missing baseline covariates will be replaced using mean imputation. We used mean imputation as it has been shown to give unbiased estimates and standard errors for the treatment effect in randomised trials, and will suffer only a small loss in efficiency when the amount of missing data is small [33].

3. We will analyse the three components that form the CPG disability score at 12 months, rather than the overall CPG disability score. This will be done by performing a multivariate analysis, where each of the three components from the 12-month score are included in the model as outcomes (that is, each participant will have three outcomes). A three-level mixed-effects model will be used, with random effects for 'course’ and for participant. Treatment-by-question interactions will be included, allowing the treatment effect to vary for each of the three components. An overall treatment effect for CPG disability at 12 months will be estimated using the *lincom* function in Stata (StataCorp, College Station, TX, USA) to combine the treatment estimates from the three separate components. As above, missing baseline covariates will be replaced using mean imputation.

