### Analysis of primary outcome

The primary outcome (CPG disability at 12 months) will be analysed using a mixed-effects linear regression model, with a 'group-based learning course’ as a random effect. Restricted maximum likelihood (REML) will be used. The model will include site of recruitment, age, gender, HADS depression score, and CPG disability at baseline as covariates.

All participants who completed at least one of the three questions that form the CPG disability score at either 6 or 12 months will be included in the analysis. Participants who did not fill out any portion of the CPG disability score at both 6 or 12 months will be excluded from the analysis.

Multiple imputation (MI) [28] will be used to account for participants who have an observed outcome at 6 months, but are missing the outcome at 12 months, as well as for participants who completed some, but not all, of the questions on the CPG disability score at 12 months. A total of 20 imputations will be performed, and results will be combined using Rubin’s Rules [28]. Only participants included in the analysis will be included in the imputation model. The imputation model will include the three questions that form the CPG disability score at baseline, 6 months, and 12 months, as well as the site of recruitment, age, gender, the HADS depression score at baseline, and employment status (employed or in full-time education versus not employed or in full-time education) (14 variables in total). We chose to include these variables in the imputation model because they will be included in the analysis model (CPG disability score at baseline, 6 months, and 12 months, site of recruitment, age, gender, and HADS depression score at baseline) or because we felt they may be predictive of missingness (employed or in full-time education versus not employed or in full-time education). Imputation will be performed separately within each treatment group [29]. In the intervention group, multilevel imputation will be performed, with 'course’ included in the imputation model as a random effect [30,31].

Missing data in any of the covariates to be adjusted for in the analysis (site of recruitment, age, gender, HADS depression score, CPG disability and baseline) will be accounted for at the same time as missing data in the CPG disability score at 6 or 12 months, as these variables will be included in the same imputation model.

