#### Participants with no completed follow-ups

The primary analysis has assumed that the excluded participants (those not completing any questions on the CPG disability questionnaire at both 6 and 12 months) were missing-at-random (that is, they were missing based on the covariates included in the analysis model). To assess the robustness to departures from this assumption, the primary outcome will be assessed under a range of missing-not-at-random scenarios. This will be done using the formula

$$\Delta =\Delta_{\mathrm{primary}}+Y_{1}P_{1}-Y_{2}P_{2}$$

where ∆ is the treatment effect under the missing-not-at-random scenario, ∆_primary_ is the treatment effect from the primary analysis, Y_1_ and Y_2_ are the assumed mean responses for participants with missing data in treatment groups 1 and 2 respectively, and P_1_ and P_2_ are the proportion of participants who were excluded from the analysis in groups 1 and 2, respectively. The standard error for ∆ is assumed to be approximately equal to the standard error for ∆_primary._ Y_2_ will be varied between 10, 25, 50, 75, and 90, and for each value of Y_2_, Y_1_ will be set to Y_2_ - 10, Y_2_, and Y_2_ + 10. For example, for Y_2_ = 25, Y_1_ will vary between 15, 25, and 35.

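### Sensitivity analysis 1 adds predictors of loss to follow-up to an imputation model that leaves out participants with no follow-up, so it reassures only in part

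*SAP article*

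**What the plan says.** Under *Analysis of primary outcome*, the SAP article sets the population: "Participants who did not fill out any portion of the CPG disability score at both 6 or 12 months will be excluded from the analysis". It sets the same limit on the imputation: "Only participants included in the analysis will be included in the imputation model". The imputation model has 14 variables. One is employment status, chosen because it might predict missingness; it is not a covariate in the analysis model.

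Under *Method of accounting for missing data*, three sensitivity analyses are planned "to assess the robustness of the results to other methods of account for missing data". The first reads: "We will determine which baseline covariates are associated with loss to follow-up and include them in the imputation model". The next sentence keeps the analysis model and places the extra covariates in the imputation model only. No change of population is mentioned, and loss to follow-up is not defined.

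Under *Participants with no completed follow-ups*, the plan states what it assumes for the excluded group, namely that they "were missing-at-random (that is, they were missing based on the covariates included in the analysis model". It then says how that will be examined: "To assess the robustness to departures from this assumption, the primary outcome will be assessed under a range of missing-not-at-random scenarios".

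**The concern.** Baseline variables that predict loss are most useful for the participants who are completely lost, because nothing else is known about them after randomisation. Sensitivity analysis 1 looks for such variables and then uses them in a model from which those participants are absent. Neither the imputation nor the analysis model then conditions on these variables for the fully lost.

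Suppose one of these variables predicts outcome beyond the five analysis covariates, and predicts complete loss differently in the two arms. The primary estimate is then biased, and sensitivity analysis 1 can correct only the part that comes from participants with some follow-up. Agreement between the two results would say little about the fully lost.

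**Working it through.** **1. The imputation model.** Three CPG disability items at three time points give 3 × 3 = 9. Adding site, age, gender, baseline HADS depression and employment gives 9 + 5 = 14, which reproduces the plan's count. The analysis model adjusts for site, age, gender, baseline HADS depression and baseline CPG disability. Employment is therefore in the first model and not in the second.

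**2. Who is reached by what.**

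| Group | In the imputation model? | Reached by the added predictors? | Missing at random given |
|---|---|---|---|
| Seen at 6 months, not at 12 | Yes | Yes | Items, imputation covariates, added predictors |
| Some items missing at 12 months | Yes | Yes | As above |
| No item at 6 or 12 months | No | No | Five analysis covariates only |

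Sensitivity analyses 2 (complete cases) and 3 (multivariate model of the 12-month items) both rest on 12-month responses, so they do not reach the third group either. The definition of loss matters. If it means no item at both visits, the predictors are found by comparing the fully lost with the rest, then used in a model that contains none of the fully lost. If it means no 12-month score, the mismatch is partial.

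**3. Size for employment.** The documents give no loss or employment figures, so every input is assumed: 40% employed in both arms; outcome 5 points lower in the employed after adjustment; complete loss in the intervention arm 25% of employed and 10% of others; complete loss in the control arm 10% of both.

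- Employed share among those analysed, intervention: (0.40 × 0.75) / (0.40 × 0.75 + 0.60 × 0.90) = 0.30 / 0.84 = 0.357.
- Employed share among those analysed, control: 0.36 / 0.90 = 0.400.
- Bias = difference in shares × outcome difference = (0.357 − 0.400) × (−5) = +0.21 points. Higher scores are worse, so this is against the course.

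The bias is proportional to the residual difference: 2.5 points gives 0.11 and 10 points gives 0.43. If loss depends on employment in the same way in both arms, the shares match and the bias is zero.

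**4. Mechanism, by simulation.** The set-up was 250 trials of 403 and 300 participants, 20 imputations within arm, clustering ignored, and a true effect of −5. A baseline covariate outside the analysis model raises the 12-month score by 9 points per SD (5 directly, plus 0.5 × 8 through the 6-month score). It raises the log-odds of loss by 1 per SD, in the intervention arm only. These inputs are assumptions and deliberately strong: the employment example corresponds to 5 × √(0.4 × 0.6) = 2.4 points per SD. Bias in points, Monte Carlo standard error about 0.1:

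| Fully lost | Primary | Sensitivity 1 as written | All randomised, covariate not added | All randomised, covariate added |
|---|---|---|---|---|
| 0.4% (17% missing at 12 months only) | −0.56 | +0.10 | −0.56 | +0.14 |
| 6% | −1.02 | −0.61 | −1.02 | −0.01 |
| 12% | −1.59 | −1.21 | −1.60 | −0.12 |
| 22% | −2.13 | −1.76 | −2.14 | +0.10 |

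As written, 0.61/1.02 = 60%, 1.21/1.59 = 76% and 1.76/2.13 = 83% of the bias remains at 6%, 12% and 22% fully lost. With almost nobody fully lost, the analysis works. Widening the population without the covariate achieves nothing, so both changes are needed.

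**The case against.** The strongest reply is that the plan never asks sensitivity analysis 1 to deal with the fully lost. Its stated aim is robustness to the method of handling missing data, and it is a proper check for participants seen only at 6 months and for partial responders. The fully lost have their own section, with scenarios in which the assumed means differ between arms by up to 10 points either way. That stands. A reader might infer that the plan ignores this group, or that sensitivity analysis 1 fails at a task set for it; the text supports neither. What the reply leaves open is that the scenarios vary assumed means and do not test missing at random given more covariates. Their formula also appears not to weight the primary effect by the proportion observed, but that is a separate point which this fix would not repair.

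A reader might also conclude that sensitivity analysis 1 would be falsely reassuring. In the simulation it moves the estimate by about 0.4 points whenever there is material complete loss (for example 1.02 − 0.61 = 0.41), so it does signal sensitivity, though incompletely.

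It may also be tempting to ask for course attendance in the intervention-arm imputation. The document gives no attendance or loss figures to show that it predicts non-response. Attendance is post-randomisation and exists in one arm only, so keeping to baseline covariates is a defensible choice.

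Finally, carrying the restricted population into sensitivity analysis 1 is inferred. The sentence "The analysis model will be the same as that for the primary analysis, except for the inclusion of additional covariates" goes on to place those covariates in the imputation model, and it speaks of the analysis model, not the population. The inference is the natural one, but it is not stated.

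**Conclusion.** The point holds in a limited form. Sensitivity analysis 1 gives partial reassurance: it covers incomplete follow-up, and it leaves the assumption for the fully lost conditioned on five covariates, without employment or any newly found predictor. No listed analysis fills that gap.

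The illustrated size is small, about 0.2 points on a 0 to 100 scale for employment, and it depends on differential loss in one arm and a residual outcome difference that the documents do not give. The simulation's larger biases show the mechanism under a strong assumed covariate; they do not estimate this trial's bias. The primary analysis need not change. This is a cheap improvement to one sensitivity analysis.

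**What to change.** In sensitivity analysis 1, define loss to follow-up, saying whether it means no item at both visits or no complete 12-month score. State that imputation in this analysis covers all 703 randomised participants (403 + 300), still within arm and with course as a random effect in the intervention group. Use the 14 primary imputation variables, including employment, plus the baseline covariates found to predict loss. Keep the analysis model and the primary analysis as they are. If the wider population is not wanted, the minimum is to say that this analysis covers only participants with some follow-up.

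The cost is a change of wording and slightly more Monte Carlo noise from imputing people with baseline data only. Using more than 20 imputations in this analysis would reduce that noise.

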#### Participants with no completed follow-ups

The primary analysis has assumed that the excluded participants (those not completing any questions on the CPG disability questionnaire at both 6 and 12 months) were missing-at-random (that is, they were missing based on the covariates included in the analysis model). To assess the robustness to departures from this assumption, the primary outcome will be assessed under a range of missing-not-at-random scenarios. This will be done using the formula

$$\Delta =\Delta_{\mathrm{primary}}+Y_{1}P_{1}-Y_{2}P_{2}$$

where ∆ is the treatment effect under the missing-not-at-random scenario, ∆_primary_ is the treatment effect from the primary analysis, Y_1_ and Y_2_ are the assumed mean responses for participants with missing data in treatment groups 1 and 2 respectively, and P_1_ and P_2_ are the proportion of participants who were excluded from the analysis in groups 1 and 2, respectively. The standard error for ∆ is assumed to be approximately equal to the standard error for ∆_primary._ Y_2_ will be varied between 10, 25, 50, 75, and 90, and for each value of Y_2_, Y_1_ will be set to Y_2_ - 10, Y_2_, and Y_2_ + 10. For example, for Y_2_ = 25, Y_1_ will vary between 15, 25, and 35.

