### Outcomes

#### Primary outcome

The primary outcome was the pain-related disability score (which is a subscale of the Chronic Pain Grade questionnaire (CPG disability) [3]) at 12 months post-randomisation.

The three questions in this subscale assess the extent to which the participant’s pain has, in the previous 6 months: (i) interfered with their ability to perform their daily activities; (ii) changed their ability to take part in recreational, social, and family activities; and (iii) changed their ability to work. Each of the three questions is rated on a scale of 0 to 10, with 0 reflecting no change or interference, and 10 reflecting extreme change or interference.

The primary outcome is the mean of these three questions, multiplied by 10; that is, if X1, *X*2, and X3 represent the three questions, and Y represents the primary outcome, then:

$$Y=10*\left(X1+X2+X3\right)/3$$

The primary outcome is therefore recorded on a scale from 0 to 100, with higher scores reflecting larger interference or change in the participant’s ability to perform daily activities, work, or take part in recreational, social, and family activities.

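### The missing-not-at-random grid for the primary outcome limits the between-arm difference to ±10 points and seeks no tipping point; with exactly equal loss its 15 scenarios give only three results

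*SAP article*

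**What the plan says.** In the SAP article, under Participants with no completed follow-ups, the primary analysis is said to treat participants with no disability item at 6 and 12 months as missing at random. To test departures from this, "the primary outcome will be assessed under a range of missing-not-at-random scenarios". The treatment effect in each scenario is Δ = Δ_primary + Y1·P1 - Y2·P2. Y1 and Y2 are the assumed mean responses of the missing participants, and P1 and P2 "are the proportion of participants who were excluded from the analysis in groups 1 and 2, respectively".

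The grid is fully specified. Y2 "will be varied between 10, 25, 50, 75, and 90", and Y1 "will be set to Y_2_ - 10, Y_2_, and Y_2_ + 10". The SE of Δ "is assumed to be approximately equal to the standard error for" the primary effect. Under Primary outcome: "The primary outcome is therefore recorded on a scale from 0 to 100".

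The section does not say how the 15 results will be judged, and it plans no search for the departure at which the conclusion changes.

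**The concern.** A treatment contrast is biased when the missing participants differ *between* arms in a way the model does not capture. A shared level, high or low, matters much less. The grid is built the other way round: five values go to the shared level and three to the between-arm difference. At Y2 = 10 and Y2 = 90 it takes Y1 to 0 and 100, the ends of the scale, yet the arms never differ by more than 10 points. Ten points is one step on each of the three 0 to 10 questions, and the section gives no reason for stopping there.

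The trial is unmasked and only one arm is invited to a course, so non-responders could differ between arms by more than this. It is also the only missing-not-at-random check of the primary outcome in the article. The three analyses under Method of accounting for missing data change the imputation model, use complete cases, or model the three questions separately. At stake is what a reader can conclude about robustness; the primary estimate itself is unaffected.

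**Working it through.** **Inputs from the SAP article.** The formula and grid above; 403 and 300 randomised (Background); two-sided 5% level (General analysis principles).

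**Inputs that are assumptions.** Loss of 5% to 20%; residual SD 20, intracluster correlation 0.05 and 14 participants per course. The article gives none of these, nor the effect or its SE. Group 1 is taken as the intervention arm.

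**1. The plan's own example.** For Y2 = 25, Y1 = 25 - 10, 25 and 25 + 10, that is 15, 25 and 35, as the article states. Five levels times three gives 15 scenarios.

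**2. Split the shift.** Y1·P1 - Y2·P2 = Y2·(P1 - P2) + P1·(Y1 - Y2). With P1 = P2 = P the first term is zero and the shift is P·(Y1 - Y2). All 15 scenarios then give -10P, 0 or +10P:

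| Equal loss P | Distinct shifts (points) |
|---|---|
| 5% | -0.5, 0, +0.5 |
| 10% | -1.0, 0, +1.0 |
| 15% | -1.5, 0, +1.5 |
| 20% | -2.0, 0, +2.0 |

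**3. Unequal loss.** At 11% v 9% the written formula gives 15 distinct values:
- lowest (Y1 = 0, Y2 = 10): 0×0.11 - 10×0.09 = -0.9
- highest (Y1 = 100, Y2 = 90): 100×0.11 - 90×0.09 = +2.9

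Part of this spread comes from entering mean responses rather than departures from the observed means. Y1 = Y2 = 50 gives 50×0.11 - 50×0.09 = +1.0 even if both observed means are 50 and the missing are no different. Centred on assumed means of 50, the highest value is 50×0.11 - 40×0.09 = +1.9 and the lowest is -50×0.11 + 40×0.09 = -1.9.

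**4. Where the result tips.** With the assumed values and P = 0.10:

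SE = √{400 × [(1 + (14×0.9 - 1)×0.05)/(403×0.9) + 1/(300×0.9)]} = √{400 × [1.58/362.7 + 1/270]} ≈ 1.80

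With the SE held fixed, as planned, the 95% confidence interval reaches zero at |Y1 - Y2| = (z - 1.96)·SE/P, where z = |Δ_primary|/SE:

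| z of primary result | Tipping difference at 10% equal loss | Inside the grid? |
|---|---|---|
| 2.2 | 0.24×1.80/0.10 ≈ 4 | yes |
| 2.5 | 0.54×1.80/0.10 ≈ 10 (9.7) | just |
| 3.0 | 1.04×1.80/0.10 ≈ 19 | no |

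At z = 3.0 the tip moves to 12.7 points at 15% loss (outside the grid) and 9.8 at 20% (just inside).

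**The case against.** Four points on the other side deserve weight.

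- *Exactly equal loss is unlikely.* A reader might infer that merely similar loss reduces the grid to three results. It does not. The chance SE of the difference in loss at 10% is √[0.1×0.9×(1/403 + 1/300)] = 2.3 percentage points, so 11% v 9% would be ordinary, and there the written formula gives 15 values reaching +2.9. This stands, although centring cuts that range to ±1.9 and the ±10 limit remains in either case.
- *The grid can overturn a result.* A reader might infer that the check will usually report robustness whatever the data. The documents do not support that. On the assumptions above, at 10% equal loss, it overturns significant results with z up to about 1.96 + 1.0/1.80 ≈ 2.5. This stands.
- *±10P belongs to the written formula.* If the observed means are weighted in, the effect is (1 - P)·Δ_primary + P·(Y1 - Y2), so the estimate also moves by -P·Δ_primary. At z = 3.0 (Δ_primary = -5.4) and 10% loss the shifts are -0.46, +0.54 and +1.54. There are still three values, but they are not ±1. This stands.
- *Ten points is not trivial, and readers could work out the tip themselves.* On an assumed SD of 20, ten points is half an SD. The formula is linear with a fixed SE, and the article commits to reporting numbers analysed, the effect and its interval. That limits the harm, but it leaves to each reader a step the plan could take in one line.

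**Conclusion.** The point holds as a cheap improvement to the choice of scenarios; it is not an error in the primary analysis. It is certain from the text that |Y1 - Y2| never exceeds 10, that no tipping point is sought, and that with exactly equal loss P the 15 scenarios reduce to -10P, 0 and +10P. The size in points rests on assumed losses, and the tipping differences rest also on the assumed SE of about 1.8. On those assumptions a borderline result is adequately probed, while a clearer one (z = 3.0 at 10% loss) would need a difference of about 19 points, so the grid could say only that the result survived 10.

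**What to change.** Keep a few Y2 levels (for example 25, 50 and 75). Widen Y1 - Y2, for example from -30 to +30 in steps of 5, with Y1 bounded by 0 and 100. Report the difference at which the 95% confidence interval for the effect first includes zero, or first excludes it if the primary result is not significant, and state robustness up to that difference so that readers can judge whether it is plausible. The ±30 is an illustration, not a figure from the documents; at 10% equal loss it would extend the written formula's shifts from ±1 to ±3 points. Use the same grid with whichever form of the formula, centred or not, is finally applied.

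The cost is one sentence in the SAP and a few lines of arithmetic, with no new data. The downside is that the robustness statement may look less favourable.

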**Figure 1 F1:**
[figure not shown]
**Schedule of assessment.** CPG, Chronic Pain Grade (Von Korff [3]); HADS, Hospital Anxiety and Depression Scale (Zigmond and Snaith [5]); EQ-5D, Quality of life (EuroQol.org); PSEQ, Pain Self-Efficacy Questionnaire (Nicholas 1989, [4]); CPAQ, Chronic Pain Acceptance Questionnaire (McCracken [6]); HEIQ, Social integration [7]; Census global health question (ons.gov.uk/census/2011-census).

**Table 1 T1:** The Coping with Persistent Pain, Effectiveness Research into Self-management (COPERS) course content overview

**Day (10.00 am to 2.45 pm)**	**Modules**
**Day 1**	Introduction and understanding pain and acceptance
Living and dealing with pain	
	Lunch
	Activity: Art
	Mind, mood and pain
	Movement and posture, and Relaxation
**Day 2**	Dealing with unhelpful, negative thoughts and barriers to change
Doing something about your life with pain	
	Lunch
	Activity: Hand massage
	Making pain more manageable
	Movement and Relaxation
**Day 3**	Communication skills
Communication and relationships	Lunch
	Activity: Volunteering
	Movement and Relaxation
**Day 4**	The future
Follow-up (2 weeks later, 10.00 am to 12.00)	

The original sample size calculation called for 685 participants (391 in the intervention group and 294 in the control group, to be randomised in a 4:3 ratio). However, we required a sufficient number of participants in each group-based learning course to make the intervention viable; therefore, we continued recruitment until there was an adequate number of participants for each course. This led to 703 participants (403 intervention, 300 control).

Ethics approval was granted by Cambridgeshire Ethics 11/EE/04. All patients provided written informed consent prior to randomisation.

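### Every missing-not-at-random scenario gets the primary standard error, which does not suit absolute assumed scores; the effect formula and its standard error should be changed together

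*SAP article*

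**What the plan says.** The primary analysis leaves out anyone with no CPG disability item at both 6 and 12 months; such participants "will be excluded from the analysis" (SAP article, Analysis of primary outcome). The check under Participants with no completed follow-ups then computes Δ = Δ_primary + Y1·P1 − Y2·P2. Here Y1 and Y2 "are the assumed mean responses for participants with missing data in treatment groups 1 and 2 respectively". The weights P1 and P2 stand for the share of each arm that the primary analysis leaves out.

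The value for group 2 "will be varied between 10, 25, 50, 75, and 90". Each value is paired with a group 1 value 10 lower, equal or 10 higher, which makes 15 scenarios: "For example, for Y_2_ = 25, Y_1_ will vary between 15, 25, and 35". In all of them the standard error of Δ "is assumed to be approximately equal to the standard error for" Δ_primary.

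**The concern.** Y1 and Y2 are absolute scores on the 0 to 100 scale, not differences from what was observed. If an excluded fraction P is given a fixed score, the mean over everyone randomised puts weight 1−P on the analysed data, which lowers its variance. It also carries the sampling error of the excluded fraction multiplied by the gap between the assumed and observed means, which raises the variance as the gap grows. One constant standard error can follow neither change.

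The purpose of the check is to show whether the primary conclusion survives, and General analysis principles commits to 95% intervals and two-sided P values at 5%. If the error bars do not respond to the scenario, the check can look more reassuring at the extremes than it should.

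**Working it through.** **Inputs from the SAP article.** 403 intervention and 300 control participants randomised (Background, text after Table 1); the score grid above; the 0 to 100 scale (Primary outcome).

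**Assumed, because the article does not give them.** Equal exclusion P of 5, 10, 15 or 20%; means of those analysed M1 = 47 and M2 = 50; residual SD after adjustment 20, 25 or 28; no inflation for clustering or imputation. The plan's own figure, a ratio of about 1, is an assumption and cannot be reproduced.

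**1. Target.** The all-randomised contrast is (1−P1)M1 + P1Y1 − (1−P2)M2 − P2Y2. With the Y values fixed and the excluded proportions subject to sampling error, its variance is the sum over arms of

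(1−Pk)²·vk + (Yk−Mk)²·Pk(1−Pk)/nk,

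where vk is the variance of the analysed mean and nk the number randomised.

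**2. One case in full: P = 15%, SD 20, Y1 = Y2 = Y.**
- v1 = 400/(403×0.85) = 1.168 and v2 = 400/(300×0.85) = 1.569. The sum is 2.736, so the primary SE is 1.654.
- First term: 0.85² × 2.736 = 1.977.
- Y = 50: add 3²×0.1275/403 = 0.003 and 0. SE = √1.980 = 1.407, ratio 0.851.
- Y = 10: add 37²×0.1275/403 = 0.433 and 40²×0.1275/300 = 0.680. SE = √3.090 = 1.758, ratio 1.063.
- Y = 90: add 43²×0.1275/403 = 0.585 and 0.680. SE = √3.242 = 1.801, ratio 1.088.

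A simulation of 20,000 trials gave SDs of 1.77, 1.41 and 1.80 at Y = 10, 50 and 90, against a mean stated SE of 1.65.

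**3. Ratio of correct to stated SE at Y = 10 / 50 / 90.**

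| P | SD 20 | SD 25 | SD 28 |
|---|---|---|---|
| 5% | 1.035 / 0.950 / 1.046 | 1.005 / 0.950 / 1.013 | 0.994 / 0.950 / 1.000 |
| 10% | 1.055 / 0.900 / 1.075 | 1.002 / 0.900 / 1.015 | 0.982 / 0.900 / 0.993 |
| 15% | 1.063 / 0.851 / 1.088 | 0.991 / 0.850 / 1.009 | 0.964 / 0.850 / 0.979 |
| 20% | 1.059 / 0.801 / 1.089 | 0.973 / 0.800 / 0.995 | 0.941 / 0.800 / 0.958 |

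With a common mean M the ratio is (1−P)√(1 + P((Y−M)/SD)²). It exceeds 1 only when |Y−M|/SD is above 1.47, 1.53, 1.60 or 1.68 for P = 5, 10, 15 or 20%. A gap of 40 points is 2.0 SDs at SD 20, 1.6 at SD 25 and 1.43 at SD 28, so the SD settles what happens at the ends.

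**4. Test statistic, equal P and Y1 = Y2.** The printed Δ equals Δ_primary with its own SE, so z is the primary z in every scenario. The all-randomised effect is (1−P)·Δ_primary, so printed z over correct z is ratio/(1−P). At Y = 50 this is 1.00. At the ends it runs from 0.994/0.95 = 1.05 (SD 28, P 5%, Y = 10) to 1.089/0.80 = 1.36 (SD 20, P 20%, Y = 90).

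**5. Changing one piece alone, mid-grid, P = 15%.** With the printed Δ over the smaller SE, z is inflated by 1/0.85 = 1.18, so a primary z of 1.67 (P about 0.096) becomes 1.96. With the all-randomised effect over the unchanged SE, z is cut by 0.85, so a primary z between 1.96 and 1.96/0.85 = 2.31 (P from 0.05 down to 0.021) looks lost. Neither is right.

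**6. Offsets instead of scores.** If the excluded differ from the analysed mean by d, the arm mean is M + P·d and, for equal P and d, the ratio is √(1 + d²P(1−P)²/SD²). For d = 10, P = 15%, SD 20 this is √(1 + 100×0.15×0.7225/400) = 1.01. For d = 40 it is √1.4335 = 1.20.

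**7. Point estimate.** The printed Δ minus the all-randomised contrast is P1M1 − P2M2. With exclusion of 15% and 10% this is 7.05 − 5.00 = +2.05 points; with 10% and 15% it is 4.70 − 7.50 = −2.80 points.

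**The case against.** The strongest reply is that the plan's standard error fits the expression it prints. Y1 and Y2 are constants and, if the observed proportions are also taken as fixed, the added terms have no variance, so the standard error of Δ equals that of Δ_primary exactly. The plan also calls the equality approximate. Both points stand. They do not rescue the check, because the printed expression is not the effect among all randomised, and the number excluded is itself a random result of the trial.

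Two stronger readings are tempting, and the article supports neither.

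- A reader might infer that the intervals are always too wide in the middle of the grid and too narrow at the ends. That pattern needs the all-randomised contrast, random proportions, and an SD and means that the article does not give. With SD 28 the ends are not too narrow. With proportions held fixed the ratio is 1−P everywhere. With the printed formula and random proportions, the stated SE is too small throughout: at P = 15% and SD 20 the ratios are 1.01, 1.08, 1.30, 1.59 and 1.79 across the five scores.
- A reader might infer that a primary P value between 0.021 and 0.05 would be lost mid-grid. It would not: with equal exclusion and equal scores, the printed effect and standard error are the primary ones. That loss would appear only if the effect were corrected and the SE sentence kept.

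It is also fair to say that the effect formula is the larger fault, with errors of 2 to 3 points when exclusion differs by 5 percentage points between arms. This is why the standard error should not be revised by itself.

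**Conclusion.** The point holds in a limited form. A constant standard error does not match absolute assumed scores. The firm part is that, for an all-randomised contrast, the correct standard error is about (1−P) times the primary one when the assumed score is near the analysed mean, whatever the SD. How far it rises at the ends cannot be settled from the article. With means 47 and 50 and P of 5% to 20%, the end ratios are 1.04-1.09 at SD 20, 0.97-1.02 at SD 25 and 0.94-1.00 at SD 28.

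The practical consequence is at the ends. With equal exclusion and equal scores, the printed test statistic does not move, and there it overstates the evidence by about 5% to 36%. Mid-grid it is right. These figures assume random exclusion proportions and no clustering, and they cover Y1 = Y2. The 10-point differences between arms widen the ratio to 0.85-1.14 at P = 15% and SD 20. This is a worthwhile correction to a secondary check; the primary analysis is untouched.

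**What to change.** Make one change with two parts. Replace the printed Δ by (1−P1)M1 + P1Y1 − (1−P2)M2 − P2Y2, with M1 and M2 the adjusted arm means from the primary model. Replace the constant-SE sentence by the scenario-specific variance in step 1. Build each interval and P value from that pair. If the adjusted arm means are appreciably correlated through shared covariates, include their covariance. A bootstrap of the whole calculation, resampling courses in the intervention arm and individuals in the control arm, is an alternative that also allows for exclusion clustering by course. Do not change the standard error alone.

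Alternatively, redefine Y1 and Y2 as modest offsets from the analysed-arm means and restate the grid on that scale. The constant standard error may then stay as an approximation (ratio 1.01 for a 10-point offset in step 6), though not for offsets as large as 40.

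Cost: the first option is a short rewording, but adjusted means and variances by arm must be extracted from the primary model and combined over the 20 imputations. The bootstrap is heavier, because each resample repeats the multilevel imputation. The offset option costs only wording and a new grid.
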